### Randomization

A list of consecutive numbers (from 1 to 78) will be generated prior to recruitment, and each of these numbers will be assigned randomly to one of the three study groups (Control Group, Mobilization Group and Pressure Group) using a computer program (www.random.org).

Without any prior knowledge of the list generated, the physiotherapist responsible for recruitment and initial assessment will assign a consecutive number to each subject participating in the study.

The physiotherapist performing the intervention will be the only one with access to the list generated by the computer program. This physiotherapist cannot be blinded due to using manual techniques and he/she will know which group the subject has been assigned to by referring to the number assigned by the evaluator.

The concealment and blinding of the assignment will therefore be assured, since the physiotherapist performing the recruitment will not know which group the subject will be assigned to.

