### Sample size calculation

The required calculation of the sample size was performed for all outcome variables, for a two-tail test, using a web application (Granmo v7.12) from the Mar Institute of Medical Research Foundation (https://www.imim.es/ofertadeserveis/software-public/granmo/). The statistics needed for the calculation were determined based on three studies: the pilot study by González-Rueda et al. [16] provided statistical data about pain intensity in a similar population and with similar techniques to those used in this study, and those by Izquierdo et al. [17] and Dunning et al. [18] comparing different manual techniques in patients with chronic mechanical neck pain provided statistical data about Neck Disability Index (NDI), range of active mobility an Headache Impact Test. The highest value obtained, using an alpha risk of 0.05 and a beta risk of 0.20 with an estimated follow-up loss of 15%, was 26 subjects per group. As there will be three study groups (the Control Group, the Mobilization Group and the Pressure Group) the total sample size will be 78 subjects.

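### The stated allocation rule does not fix 26 per group, and concealment is called assured although it depends only on the treating therapist not disclosing the list

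*Protocol article*

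**What the plan says.** The Sample size calculation section reports that the highest requirement, "using an alpha risk of 0.05 and a beta risk of 0.20 with an estimated follow-up loss of 15%, was 26 subjects per group", and so "the total sample size will be 78 subjects".

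The Randomization section describes a list of numbers 1 to 78 made before recruitment, in which "each of these numbers will be assigned randomly to one of the three study groups" by a computer program. Neither this section nor any other part of the article states an allocation ratio, a block size or a fixed count per group.

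On custody of the list: "The physiotherapist performing the intervention will be the only one with access to the list generated by the computer program". A different physiotherapist recruits, does the baseline assessment and hands out the numbers in order without having seen the list. The treating therapist reads each participant's group from that number. The section concludes: "The concealment and blinding of the assignment will therefore be assured". The reason it gives is that the recruiter does not know the group. The Intervention section repeats that the treating therapist alone holds the list, and adds that this person is blinded to the assessment results.

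**The concern.** There are two separate gaps between what the text claims and what its procedure delivers.

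1. **Group sizes.** The power calculation presumes 26 in each group. The allocation rule restricts nothing, so taken literally it is simple randomisation, under which group sizes vary by chance. Comparisons that involve the smallest group then have less power than planned.

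2. **Custody of the list.** The holder of the full list is unblinded and treats every participant. Because numbers are used in order, anyone who knows the last number used and holds the list knows the next allocation before that person is enrolled. If this reached the recruiter, it would matter twice: the same physiotherapist decides eligibility (including the flexion-rotation test, which depends partly on the examiner's end feel) and performs every outcome assessment.

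**Working it through.** **Inputs.** From Sample size calculation: 26 per group, 78 in total, two-sided alpha 0.05, power 0.80, loss 15%. From Randomization: each of 78 numbers assigned at random to one of three groups, with no restriction stated. No effect size or standard deviation is given ("The statistics needed for the calculation were determined based on three studies"), so the base sample size cannot be recomputed.

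**The plan's own figures.** 3 × 26 = 78. Also 22 / (1 − 0.15) = 25.9, which rounds up to 26, so 26 per group is consistent with 22 evaluable per group.

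**Group sizes if each number is assigned independently with probability 1/3** (exact multinomial):

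- SD of one group's size = √(78 × 1/3 × 2/3) = 4.16, around a mean of 26.
- P(26/26/26) = 78! / (26!³ × 3⁷⁸) = 0.0105.
- Expected smallest group, summing min(a, b, c) × P(a, b, c) over all splits = 21.7.
- P(smallest group ≤ 22) = 57.4%; P(≤ 20) = 27.1%; P(≤ 18) = 9.9%. All are before any loss.
- P(largest minus smallest ≥ 10) = 38.4%.

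Under a random permutation of 26 + 26 + 26 labels, P(26/26/26) = 1.

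**What this costs in power.** Assume the standardised effect that gives 80% power with 22 evaluable per group: d = (1.960 + 0.842) × √(2/22) = 0.845. Remove 15% from every group and use power = Φ(d / √(1/(0.85a) + 1/(0.85b)) − 1.960) for a pair randomised a v b:

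| Randomised sizes | Pairwise power | Change from 26 v 26 |
|---|---|---|
| 26 v 26 | 80.2% | – |
| 22 v 26 | 76.7% | −3.5 points |
| 20 v 26 | 74.5% | −5.7 points |
| 22 v 22 | 73.3% | −6.9 points |

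Averaged over all splits, pairwise power is 79.2%, a loss of 80.2 − 79.2 = 1.0 point. A given pair falls below 75% in 11.5% of draws.

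**Concealment, step by step.** No arithmetic applies.

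- The recruiter screens, takes consent, assesses and numbers without seeing the list. This is real separation of roles.
- The list holder has no stated part in screening, consent or numbering.
- The list holder nevertheless has all future allocations in open form, and numbers are consecutive.
- The reason offered for assurance, that the recruiter does not know the group, is the result wanted. The only thing that brings it about is that the list holder does not pass the information on.

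**The case against.** **The wording does not say that numbers are assigned independently or one by one.** A closed list of 78 numbers, read with the 26 per group of the sample size section, also fits a random split into three sets of 26. This stands. Every probability above is conditional on the independent reading. The defect is that the text does not fix the sizes, not that unequal groups are certain.

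**Even on the independent reading the harm is small.** Simple randomisation is a valid method, and chance differences in group size cause no bias. The average loss is about 1 point of power. The planned intention-to-treat analysis with last observation carried forward would also keep participants whom the calculation above removes, which raises all the power figures. This stands too. What remains is an avoidable risk for a single pair in an unlucky draw.

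**Concealment concerns the person who enrols, and that person does not see the list.** A reader might infer that the treating therapist can steer the order or timing of enrolment, and that the trial therefore carries a selection bias beyond repair. The documents do not support that. They give the therapist no role in enrolment, so steering would require disclosing the list or intervening, and nothing suggests either. Nor do they describe how the two physiotherapists work together; they name only a single recruiting service.

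**Envelopes and an independent preparer may appear in the full protocol.** Their absence from an article is no fault. But the custody rule here is stated, not omitted: the therapist is said to be the sole person with access to the whole list.

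**Conclusion.** The concern holds in a limited form, in two parts.

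- The allocation rule as written does not secure the 26 per group on which the sample size rests. If assignment is independent, exact balance arises about 1% of the time and the smallest group is expected to be 21.7. The power cost is about 1 point on average and 5 points or more for a given pair in roughly one draw in nine (11.5%). These power figures rest on an assumed effect calibrated to 80% at 22 evaluable per group and on 15% loss in every group.
- Concealment is protected by separation of roles but depends only on one unblinded person not disclosing an open list. Calling it assured claims more than the procedure supports. It does not follow that concealment is absent or that enrolment will be biased, and no size can be put on this part.

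**What to change.** Generate the list as one random permutation of 26 + 26 + 26 labels, or in permuted blocks of varying size (each a multiple of three, together summing to 78), and state this in the Randomization section. Have it prepared by existing staff who do not recruit, evaluate or treat. Release each allocation to the treating therapist only after that participant's consent and baseline assessment, for example in sequentially numbered, opaque, sealed envelopes. The therapist then no longer holds the full list.

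The cost is minor clerical work and an edit to one section. The drawback is that with fixed totals the therapist, who knows all earlier allocations, can deduce the last few; the 78th is always determined by the first 77. Blocks raise the same issue at the end of a block, which varying the size reduces.

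The Intervention section describes the list partly in the past tense, so the list may already exist. If it is in use, do not regenerate it. Instead, soften the statement that concealment is assured, and report the allocation method actually used and the resulting group sizes.

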### Variables studied

The physiotherapist responsible for recruitment (Master’s Degree in Orthopaedic Manual Therapy and 7 years of experience in this field) will perform all the evaluations for this study, and will remain blinded as regards the group that the subject has been assigned to at all times.

Table 1 shows the sociodemographic variables and the values that each one may have. The following variables: age, sex, duration of symptoms, work, work with lifting, work with sustained focal distance, housework, use of mouthguard, presence of dental prosthesis, visual problems, presence and frequency of headaches and analgesic and anti-inflammatory medication will be recorded at the beginning of treatment by anamnesis.

**Table 1 Tab1:** Independent sociodemographic variables

Variable	Values
Age	Years
Sex	Man/Woman
Duration of symptoms	Months
Work	Employed/Unemployed
Work with lifting	Yes/No/Varied
Work with sustained focal distance	Hours
Housework	Hours
Mouthguard	Yes/No
Dental prosthesis	Yes/No
Visual problems	Yes/No
Headaches	Yes/No
Headache frequency	Daily - Weekly - Monthly - Quarterly - Annual
Medication	Yes/No

Table 2 shows the outcome variables, the evaluation period for each one and the measuring instrument used. All evaluations will be performed by a single physiotherapist, who will also be responsible for the recruitment, and who will be blinded throughout the evaluation period as regards the group assigned to each subject.

**Table 2 Tab2:** Outcome variables

Outcome variables	Evaluation period			Measuring instrument
	Baseline	Post-treatment	Three months post-treatment	
Intensity of neck pain (main outome)	X	X	X	VAS
Neck disability	X	X	X	NDI
Overall cervical range of motion	X	X	X	CROM
Upper cervical range of motion	X	X	X	CROM
Headache intensity	X	X	X	HIT-6
Rating of clinical change		X	X	GROC scale

Main outcome will be the intensity of pain in the cervical region measured with a visual analog scale (VAS) from 0 to 100 mm in length, with the extremes defined as “no pain” (0) and “the worst pain imaginable” (100) and without any intermediate points. The test-retest reliability has proven to be good (ICC 0.92) [21].

Neck disability will be measured using the Neck Disability Index (NDI). This is a self-applied questionnaire consisting of 10 sections with 6 possible answers representing six progressive levels of functional disability, rated from 0 to 5, with 0 being the first level and 5 the last level of each section. The total score ranges from 0 to 50 points, with higher scores indicating greater disability. At least 8 of the 10 sections must be answered for the score to be calculated. The test-retest reliability has proven to be adequate (ICC 0.97) and it has been validated for the Spanish language [22].

The overall range of active mobility in the cervical region will be evaluated in a sitting position with the vertical back resting on the backrest of the chair [23]. Flexion, extension, right and left inclination and left and right rotation will be measured. A CROM device with good intra- and interexaminer reliability (ICC > 0.80) [24] will be used in all the measurements. Two measurements will be made for each movement, and the result will be the mean of the two measurements.

The range of active mobility in flexion and extension of the upper cervical region will be measured in a standing position with the back against a wall. The flexion-rotation test [25, 26], which has proven to have high levels of intra- and interexaminer reliability (ICC 0.98) [27] will be used to measure the range of motion in rotation in the upper cervical region. To perform the FRT, the subjects position themselves in the supine position and the evaluator passively takes the patient’s cervical spine to its maximum flexion and then rotates the head to the right and left side with the occiput resting against the evaluator abdomen. The movement stops at whichever situation occurs first, either the subject presents symptoms, or the evaluator reaches the end of the range of motion and finds a hard end feel [12]. As in the measurement of overall cervical mobility, a CROM device will be used for all the movements of the upper cervical region, and two measurements will be performed for each movement, with the result being the mean of the two measurements.

Headache intensity is measured by the validated Spanish version of the HIT-6 (Headache Impact Test) questionnaire [28]. This questionnaire consists of 6 items (intensity of pain, social functioning, role functioning, vitality, cognitive functioning and psychological disorder), which each have five response options (Never: 6 points, Rarely: 8 points, Sometimes: 10 points, Very often: 11 points, Always: 13 points), with a score range of 36-78 points. It has proven to have good test-retest reliability (ICC 0.80) [29, 30].

The patient’s rating of clinical change will be evaluated with a Global Rating of Change Scale (GROC scale) [31]. This is a scale of 15 items, of which 7 are improvement and 7 are deterioration, and with 1 central item with no clinical change. Values from the fourth item of improvement or deterioration will be considered clinically significant, values between the three item of improvement and the three item of deterioration will be considered as no clinically significant changes [32]. The test-retest reliability has proven to be good (ICC 0.90) [33].

Additionally, changes in medication (more, less or the same dose) and the presence of exacerbations and/or recurrence will be recorded by anamnesis 3 months after the treatment period. Exacerbation is considered the isolated process of increased pain which patients control themselves using the patterns learned, and exacerbations requiring further medical advice will be considered recurrences.

### Intervention

Intervention will be provided by a different physiotherapist (PhD, with more than 13 years of experience in the field of Orthopaedic Manual Therapy) who was the only person having the random allocation list and implemented the treatment according to the group assigned to the participant’s number by the computer program, blinded to the results of the assessment.

The three groups will receive a common protocolized treatment and additionally, the translatory dorsal glide mobilization technique (TDGM) will be applied to the Mobilization Group and the pressure maintained suboccipital inhibition technique (PMSIT) will be applied to the Pressure Group.

#### Control group procedure

The Control Group will only receive the protocolized intervention in 15 daily sessions (Monday through Friday) for 3 weeks. Each session consists of the application of surface thermotherapy (20′ of infrared), an educational discussion (10′ of education about the disease and movement management in the initial sessions, and to answer new questions raised by the patients in subsequently sessions) and kinesitherapy under the physiotherapist’s supervision (30′ of self-stretching of cervical muscles and dorsal flexibility exercises). At the end of the 3 weeks of treatment, patients are instructed to perform self-stretching and dorsal flexibility exercises at home until the final evaluation at 3 months.

#### Mobilization group procedure

The Mobilization Group will receive the same protocolized treatment and the same instructions as the Control Group, and will also receive 6 sessions (two sessions per week on alternate days) of the translatory dorsal glide mobilization technique (TDGM C0-C1). The technique will be applied for 5 min per session in consecutive cycles of dorsal pushes for about 15 s resting for about 3-5 s, until the first marked resistance felt by the therapist has been exceeded, which would be equivalent to grade III according to the Kaltenborn’s diagram of degrees of movement [34]. Usually this technique is not painful, nevertheless when patient refers pain, pressure is adjusted until a non painful sensation.

The subject will be in supine position and the physiotherapist will position the proximal hand, taking the patient’s occipital in the palm, and the other hand under the posterior arch of the atlas, keeping the fingers extended for greater stability. With the proximal hand, the physiotherapist will position the head in a slight ventral flexion, a slight contralateral tilt and ipsilateral rotation towards the hypomobile atlanto-occipital joint, and will exert pressure with the shoulder on the patient’s forehead in a dorsal direction so that the occipital condyle slides dorsally on the atlas, which remains stable due to being supported in the distal hand (Fig. 2).

**Fig. 2 Fig2:**
[figure not shown]
Suboccipital translatory dorsal glide mobilization (TDGM) C0-C1 technique

#### Pressure group procedure

The Pressure Group will receive the same protocolized treatment and the same instructions as the Control Group and will also receive 6 sessions (two sessions per week on alternate days) of the pressure maintained suboccipital inhibition technique (PMSIT) [14, 16] applied for 5 min.

The subject will be in supine position and the physiotherapist will be seated at the head of the patient with the forearms resting on the table. The physiotherapist locates the suboccipital region, and applies pressure in a ventral direction in that region by flexing the metacarpophalangeal joints at 90° from fingers III-IV, while the rest of the patient head reposes on the palms of the hands, enabling the pressure to be regulated as perceived by the therapist while performing the technique (Fig. 3).

**Fig. 3 Fig3:**
[figure not shown]
Pressure maintained suboccipital inhibition technique (PMSIT)

### Statistical analysis

The data analysis will be performed after the data for the entire sample has been collected, using the SPSS Stadistic® v.20.0 software package. The significance level is established at 0.05 and the limits of the confidence interval at 95%.

A descriptive analysis of the baseline characteristics of the sample will be performed. All the quantitative variables will be analysed using the Kolmogorov-Smirnov test with Lilliefors corrections, to ascertain whether they follow a normal distribution. The initial homogeneity between the groups will be also analysed (ANOVA or Kruskal-Wallis depending of the normality of data distribution). According to the results of the homogeneity and normality analysis, parametric or non-parametric statistics will be used for the within and between-group analysis.

Within-group results will be analysed using repeated measures ANOVA (when initial homogeneity and normality of data distribution were found), Friedman test (when initial homogeneity but not normality of data distribution were found), or a linear mixed model adjusted for the baseline values when not initial homogeneity were found.

Between-group results will ve analysed using ANOVA with Bonferroni post hoc statistic (when initial homogeneity and normality of data distribution were found), Kuskall-Wallis test (when initial homogeneity but not normality of data distribution were found) or a linear mixed model adjusted for the baseline values, when not inicial homogeneity were found.

The principles of intention-to-treat analysis will be used. In the event of follow-up losses, the outcome variables that have not been recorded will be completed with the last data recorded for each of these variables (Last-Observation-Carried-Forward-Analysis).

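### Pre-tests of baseline homogeneity and normality choose each outcome's between-group analysis, so baseline is usually left unadjusted and the main VAS analysis is not fixed in advance

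*Protocol article*

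**What the plan says.** The Statistical analysis section of the protocol article sets two pre-tests and makes the analysis depend on them.

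- Normality: "All the quantitative variables will be analysed using the Kolmogorov-Smirnov test with Lilliefors corrections".
- Baseline homogeneity of the three groups: ANOVA or Kruskal-Wallis, depending on normality.
- The switch: "According to the results of the homogeneity and normality analysis, parametric or non-parametric statistics will be used for the within and between-group analysis".

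Three between-group routes follow:

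1. Homogeneous and normal: ANOVA with Bonferroni post hoc comparisons.
2. Homogeneous but not normal: "Kuskall-Wallis test (when initial homogeneity but not normality of data distribution were found").
3. Not homogeneous: "a linear mixed model adjusted for the baseline values, when not inicial homogeneity were found".

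The within-group analysis follows the same three-way rule, with repeated measures ANOVA, Friedman or the mixed model. On level, the section says "The significance level is established at 0.05 and the limits of the confidence interval at 95"%; no other level is given for the pre-tests. Table 2 shows a baseline measurement for every outcome except GROC and names neck pain intensity on the VAS as the main outcome. The section does not say whether the unadjusted tests use follow-up scores or change from baseline.

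**The concern.** In a randomised trial a significant baseline difference is a chance event, so a homogeneity test says little about whether adjustment is useful. What matters is how strongly baseline predicts follow-up. A baseline-adjusted comparison removes that part of the variance whether or not the groups happen to differ at the start. Here the adjusted model is kept for the few cases where the test rejects, and the information is discarded in the rest.

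The rule is also inconsistent:

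- Non-normality rules out ANOVA, but it is ignored once homogeneity fails, because the mixed model is then used whatever the distribution.
- The within-group method is decided by a baseline comparison between groups, which has no bearing on change within a group.

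At stake are the power for the main comparison and whether its test is settled before the data are seen. As written, the VAS could be analysed in any of three ways, and different outcomes could end with different effect measures.

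**Working it through.** **Inputs from the article.** Sample size calculation: "using an alpha risk of 0.05 and a beta risk of 0.20 with an estimated follow-up loss of 15%, was 26 subjects per group", "for a two-tail test, using a web application (Granmo v7.12"), and "the total sample size will be 78 subjects", taken here as equal allocation to three arms. Pre-test and analysis level: 0.05.

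**The plan's own figure.** The 26 per group cannot be reproduced, because no effect size or SD is stated. Only the loss allowance can be followed: 22/(1 − 0.15) = 25.9, so 26. With 22 evaluable per group, 80% power at two-sided 0.05 implies a standardised difference of about 0.845. If all 26 are analysed, which last observation carried forward allows, 0.79 SD gives about 80%: non-centrality 0.79 × √(26/2) = 2.85, power 0.798.

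**Assumptions.** The difference of 0.79 SD (one arm differing from the other two), normal data, and a baseline-to-follow-up correlation r of 0.3 to 0.7. None of these is in the documents.

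**How often adjustment is used.** Under randomisation the homogeneity test rejects with probability 0.05 per outcome (simulated 4.8–5.2%). About 95% of the time the unadjusted route is taken.

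**Power per pairwise comparison at 0.05/3.** The effective standardised difference is:

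- follow-up scores, unadjusted: d
- change scores, unadjusted: d/√(2(1 − r))
- baseline-adjusted: d/√(1 − r²)

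At r = 0.5 these are 0.79, 0.79/√1 = 0.79, and 0.79/0.866 = 0.912. With pooled variance and 26 per arm the non-central t gives 65.5%, 65.5% and 79.7%.

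Simulating the homogeneity switch (baseline ANOVA at 0.05 selects unadjusted ANOVA or ANCOVA; ANCOVA stands in for the mixed model at one visit) gives:

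| r | Switch, follow-up scores | Switch, change scores | Always adjusted |
|---|---|---|---|
| 0.3 | 66% | 49–50% | 70% |
| 0.5 | 66% | 66% | 79% |
| 0.6 | 67% | 77–78% | 86% |
| 0.7 | 67% | 89% | 93% |

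The loss runs from about 4 points (r = 0.3 on follow-up scores, r = 0.7 on change scores) to 26 points (r = 0.7 on follow-up scores).

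**With the normality step and rank branch included** (22 per arm, 0.845 SD, global three-group test, normal data). The full rule on follow-up scores has power 81.2%, 82.0% and 82.3% at r = 0.3, 0.5 and 0.7, against 84.5%, 91.1% and 98.2% always adjusted. On change scores it has 67.0%, 82.0% and 96.4%. Even with truly normal data, testing baseline and follow-up for normality sends about 10% of trials to the rank branch (1 − 0.95² = 9.75%).

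**Type I error.** With normal data the overall rate is about 3.7–4.9% across r = 0.3 to 0.7, on follow-up or change scores. Always adjusting gives about 5%.

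**Strongly skewed (lognormal) data**, same 22-per-arm setting. The rule goes to the rank branch in about 97–99% of trials. On follow-up scores its power is 96.4%, 96.7% and 97.1% at r = 0.3, 0.5 and 0.7, against 84.7%, 89.7% and 96.6% for the adjusted model. On change scores it is 80.0%, 90.7% and 98.5%.

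**The case against.** The strongest defence is that the plan does name a baseline-adjusted model, keeps overall false positives at or below 5%, and turns to rank tests where they may do better. Three parts of this stand. The error rate is off only on the safe side. The power loss rests on assumed inputs and can be as small as 4 points. With strong skew the rank route can have more power than the adjusted model. None of this justifies letting a test of chance imbalance decide on adjustment, or leaving the main test to be chosen from the data.

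A reader might infer more than the documents support:

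- **That the two-stage rule inflates type I error.** The overall rate is conservative.
- **That the Kruskal-Wallis route cannot show which technique is better, because no pairwise test or effect measure is named.** A condensed article commonly leaves such detail to the full plan. Nor can it be said that this route ignores baseline, since change scores are not excluded.
- **That about half of such trials would switch method for at least one outcome.** That is 1 − 0.95¹³ = 48.7%, which needs 13 independent outcomes, reached by splitting the mobility measures into single movements. Table 2 lists five baseline-measured variables, so 1 − 0.95⁵ = 22.6%, and this too assumes independence. Movements of the same neck are unlikely to be independent.
- **That one baseline-adjusted model could serve every outcome.** GROC has no baseline.

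**Conclusion.** The point holds as a defect of efficiency and pre-specification. The rule makes baseline adjustment depend on a test that rejects by chance about once in twenty times per outcome, is inconsistent in its own logic, and leaves the main VAS analysis open. With normal data, 26 per arm and 0.79 SD, the cost is about 13 points of pairwise power at r = 0.5, and between 4 and 26 points over r = 0.3 to 0.7, depending on whether follow-up or change scores are tested. These sizes rest on an assumed effect and correlation. The description of the rule and its inconsistencies does not. The documents do not support a claim of excess false positives, or of a power loss whatever the distribution.

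**What to change.** - Delete the baseline-homogeneity tests and the three-way switch. Keep a descriptive baseline table.
- For each quantitative outcome with a baseline, make the baseline-adjusted linear mixed model already in the plan, or a baseline-adjusted ANCOVA at each visit, the single primary between-group analysis. Choose one of the two now.
- Report Bonferroni-adjusted pairwise group differences with 95% confidence intervals for every such outcome.
- Check model residuals rather than raw values. If they are clearly skewed, add a rank-based or bootstrap sensitivity analysis without replacing the primary one.
- Analyse GROC separately by one pre-stated method without a baseline term.

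The cost is rewording the section before analysis; no further data are needed. The downside is that some power may be lost against a rank test if the data turn out strongly skewed.

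### Last-observation-carried-forward as the only missing-data rule can bias the group comparisons in either direction, and is undefined for GROC in patients lost before the post-treatment visit

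*Protocol article*

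**What the plan says.** The Statistical analysis section states: "The principles of intention-to-treat analysis will be used". For losses to follow-up it then fixes a single rule: "outcome variables that have not been recorded will be completed with the last data recorded for each of these variables (Last-Observation-Carried-Forward-Analysis". The rule covers every outcome, including the main one (neck pain on a 0 to 100 mm VAS), and no sensitivity analysis stands beside it. The same section names a baseline-adjusted linear mixed model, but only for groups that differ at baseline, not as a way to handle missing data.

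Loss is expected. The Sample size calculation section gives the result "with an estimated follow-up loss of 15%, was 26 subjects per group".

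Table 2 (Variables studied) schedules VAS, NDI, the two mobility outcomes and HIT-6 at baseline, post-treatment and 3 months later. The row "Rating of clinical change" (GROC) has entries only for the last two visits.

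The Discussion anticipates a VAS improvement above 2.5 cm. It treats as unknown whether a gain in mobility will last.

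**The concern.** With three visits the rule does one of two things. A patient lost before the post-treatment visit keeps the baseline value at both later visits, so the change is exactly zero. A patient lost after it has the post-treatment value repeated at 3 months, so the gain is held constant. The first sits badly with a plan that anticipates improvement over three weeks of daily sessions. The second assumes, for the patients concerned, an answer to a question that the Discussion leaves open for mobility.

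Two results are at stake: the between-group differences post-treatment and at 3 months, and whether every randomised patient can be included for GROC as intention-to-treat requires.

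**Working it through.** **The plan's own figure.** The inputs are "using an alpha risk of 0.05 and a beta risk of 0.20", "for a two-tail test", and 15% loss. The difference and SD behind the calculation are not stated, so 26 cannot be rebuilt forwards. Backwards it is consistent: 22 / 0.85 = 25.9, rounded up to 26, and 3 × 26 = 78. With 22 evaluable per group the implied standardised difference is (1.960 + 0.842) × √(2/22) = 0.845.

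**Expected losses.** 26 × 0.15 = 3.9 per group; 78 × 0.15 = 11.7 in total. The timing of loss is not stated.

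**Size of the bias.** Let p be the share of an arm lost before the post-treatment visit, q the share lost after it, and assume loss unrelated to outcome. LOCF then shifts the arm's 3-month mean by

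p × (baseline mean − 3-month mean) + q × (post-treatment mean − 3-month mean).

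The bias in a group comparison is the difference between the two arms' shifts.

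- Early loss, both arms fall 25 mm, no true difference: 25 × (0.20 − 0.10) = 2.5 mm; 25 × (0.25 − 0.05) = 5.0 mm. The arm with more loss looks worse.
- Equal early loss of 15%, true difference 17 mm: 17 × 0.15 = 2.55 mm toward zero.
- Equal late loss of 15%, effect sustained: 0 mm.
- Equal late loss of 15%, a 17 mm post-treatment difference gone by 3 months: 17 × 0.15 = 2.55 mm of false benefit.
- Equal loss, same course in both arms: 0 mm.

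The 25 mm is the Discussion's relevance benchmark, used here as an assumed fall. The 17 mm is 0.845 × 20 mm, with an assumed SD of 20 mm. The loss splits are also assumptions.

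**Simulation.** Two arms of 26, three visits, assumed SD 20 mm and within-patient correlation 0.5, loss unrelated to outcome, 20,000 runs per scenario. LOCF is compared with a t test on observed 3-month values.

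| Scenario | True 3-month difference | LOCF bias | Rejection rate, LOCF vs observed |
|---|---|---|---|
| 15% in each arm, all early, sustained | 17 mm | 2.6 mm toward zero | 64% vs 79% |
| 15% in each arm, half early, sustained | 17 mm | 1.3 mm toward zero | 75% vs 78% |
| 15% in each arm, all late, sustained | 17 mm | 0.0 mm | 85% vs 78% |
| 15% in each arm, all late, effect gone | 0 | 2.6 mm false benefit | 7.2% vs 5.0% |
| Early loss 7.5% vs 22.5%, both fall 25 mm | 0 | 3.7 mm | 9.1% vs 4.9% |
| Early loss 5% vs 25%, both fall 25 mm | 0 | 5.0 mm | 12.3% vs 4.8% |
| Equal loss, both fall 25 mm | 0 | 0.0 mm | 4.6% vs 5.0% |

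Coverage of the 95% interval under LOCF was 87.7% in the 5% vs 25% case. The observed-data analysis was unbiased throughout, as it should be when loss is unrelated to outcome.

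**Precision.** If carried values count as data, the standard error is multiplied by √(22.1/26) = 0.92. The simulation gave 5.52 against 6.00 mm when all loss was late and the effect sustained, but 6.04 against 6.00 mm when all loss was early.

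**GROC.** If none, half or all of the expected loss is early, then 0, about 6 or about 12 of 78 patients have no GROC value to carry forward.

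**The case against.** The case for leaving the rule alone has real substance, and it limits the point in five ways.

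- **Certain bias.** A reader might infer that LOCF must distort the comparison. It need not: two plausible situations give none, and equal early loss with a true effect only weakens it.
- **The 3-month result as a whole.** A reader might infer that persistence is settled by assumption. That holds only for lost patients, about 4 of 26 per group; about 22 are observed.
- **Standard errors 8% too small.** This does not hold generally. With early loss the standard error was not reduced at all. In the simulation the LOCF standard error also matched the actual spread of the LOCF estimate, so poor coverage came mainly from bias. What remains is that the gain under late loss is earned only if the carried value is a fair substitute for the missing one.
- **GROC as unusable.** The gap affects only patients lost before the post-treatment visit. Later losses have a GROC value to carry.
- **Implausible assumptions.** The article does not mention rebound, patients are chronic, and home exercises continue until the 3-month visit. A stable course is possible; it is simply not known.

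One could add that an unseen analysis plan may settle the details. That would answer a silence, but LOCF is a stated choice. Because timing and balance of loss cannot be known in advance, the benign scenarios cannot be relied on to defend it as the only method.

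**Conclusion.** The point holds in conditional form. LOCF is the sole stated rule, 15% loss is planned for, and the rule can move the group comparisons either way. Across the scenarios examined the bias ran from 0 to 5 mm on the VAS, with the largest value only under marked imbalance in early loss. These figures rest on an assumed 25 mm fall or 17 mm difference, an assumed SD and correlation, assumed timing and splits of loss, and loss unrelated to outcome; outcome-related loss was not examined. Overstated precision is a possibility when loss is late, not a general result.

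The GROC gap needs no assumption about the course of pain. It follows from Table 2 and the carry-forward rule together, and only the number affected depends on timing.

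**What to change.** Replace LOCF as the main method. For outcomes measured at all three visits, fit a likelihood-based linear mixed model for repeated measures to every observed value, with group, visit and group-by-visit terms. Include baseline as a response. If it is only a covariate, as in the baseline-adjusted model that the article names, patients with no later visit drop out of the analysis. The model needs no imputation and is valid under missing-at-random.

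Keep LOCF, or preferably delta-adjusted multiple imputation, as a sensitivity analysis only.

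For GROC, state a separate rule: analyse observed values, or multiply impute using the other outcomes. Counting missing as not improved is itself single imputation, so it belongs in a sensitivity analysis.

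The cost is more than a change of one sentence. The mixed model would replace the scheme that chooses between ANOVA, Kruskal-Wallis and Friedman tests for the outcomes measured at all three visits, and one sensitivity analysis is added. Visits, data collection and the sample size stay as they are.
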